### Plan for Sharing Individual Participant Data

Deidentified individual participant data collected during the trial will be made available 6 months after study completion, up to 5 years after the trial end date. Individual participant data may be shared with qualified researchers for scientific purposes. Access will be provided after a formal request, including the research proposal and statistical analysis plan, has been reviewed and approved by the principal and senior investigators, with a signed data sharing agreement. We will publish the study protocol, informed consent, and statistical analysis plan in a peer-reviewed journal. Requested data and clinical study reports will be provided through a secure data-sharing platform (Vivli—Center for Global Clinical Research Data).

### Ethical Considerations

This study protocol and all study forms, including the informed consent, have been approved by the IRBs of Universidad Peruana Cayetano Heredia (IRB00001014, Federalwide assurance number FWA00000525) and Hospital Nacional Cayetano Heredia. All amendments to this protocol are to be approved by both IRBs and amended on the trial registry’s platform. Participants sign an informed consent form before enrollment. Trained research staff give participants a verbal explanation regarding the rationale, main procedures of the study, and the main risks and benefits. They are also told that participation is voluntary, and participating, remaining, or withdrawing from the study does not affect the care they receive at the study center. Nevertheless, patients were informed that data collected until withdrawal could be used in our analysis. Messages sent by the research team do not contain allusions to the hospital, HIV, or ART, and participants are encouraged to use secure passwords on their cell phones. Participants received a 1-time compensation of US $6 to account for potential expenses in mobile data. Only the researchers can access participants’ personal data, and identifiable data are stored in secure platforms or locked cabinets. Findings will be published in peer-reviewed journals. This protocol adheres to SPIRIT (Standard Protocol Items: Recommendations for Interventional Trials) guidelines (Multimedia Appendix 3).

## Results

The study received funding from the School of Medicine of Universidad Peruana Cayetano Heredia in August 2022. The messaging platform was designed from December 2023 to March 2024. Enrollment began in March 2024, and as of July 2024, we have enrolled 131 participants. Data collection began with enrollment and intervention delivery for the first participant in March 2024. As of February 2025, we are in the process of data curation.

## Discussion

Guided by the application of BCTs, we hypothesize that self-designed messages may be more effective in improving adherence to ART than standardized messages. Therefore, we aim to evaluate the effectiveness of a mobile phone messaging intervention with WhatsApp to improve adherence to antiretrovirals in young people living with HIV who receive routine HIV care at a public health facility in Lima and assess if there is a difference in effectiveness between the 2 types of messages tested. In a setting with still inceptive use of mHealth, our study protocol will provide valuable information on associations between several covariables, ART adherence, and participants’ experience with our pilot mHealth intervention.

Self-designed messages offer customization features that may enhance participant engagement with the intervention and increase its efficacy [26,27]. Therefore, we expect participants in the self-designed messages arm to have improved adherence compared to the standardized messages arm. Some subgroups may benefit more from the intervention, although it is beyond the scope of this study to compare differences between study arms and potential effect size. Given the potential personal customization component, we hypothesize that the self-designed arm will have an increased median time of permanence in the study and lower loss to follow-up. We also anticipate that loss to follow-up may hinder the statistical significance of results for the primary outcome and ART adherence measured at 4, 8, and 12 weeks of intervention for both study arms.

A recent meta-analysis showed that SMS interventions improved adherence to ART, although there was considerable heterogeneity among study results [28]. The studies with greater efficacy were interactive or used bidirectional SMS, which supports our approach and is consistent with previous studies [11]. Our study uses a bidirectional platform, and participants can constantly interact with the research team through chatting. However, evidence suggests that implementing a messaging intervention in low-resource settings may be challenging owing to technical limitations, and difficulties in delivering the intervention may result in suboptimal outcomes [29]. Therefore, we established a 2-week pilot period that allows us to assess intervention delivery using the messaging platform, and having real-time data on multiple delivery indicators (messages and questionnaires scheduled for delivery, sent, received, seen, and answered by participants) allows for constantly monitoring the fidelity of intervention delivery.

In addition to the rigor of a randomized controlled trial, our study protocol has other strengths. To our knowledge, it is the first study evaluating the effectiveness of an mHealth intervention with different types of BCT-guided messages to improve adherence to ART. Our trial is conducted in a resource-constrained setting where there is much need for similar interventions and a still limited body of evidence about effectiveness. The thorough data register of our web-based study platform allows us to measure the cascade of intervention delivery, including the differentiation of messages received but unread.

The study also has limitations. First, as in many other studies, we use a self-reported measurement of medication adherence; extensive use does not assure full accuracy for outcome measurement. We will compare SMAQ results to viral load and CD4 lymphocyte measurements when available to address this. Limitations inherent to the local health system might prevent participants from having up-to-date results of these objective indicators, which restricts the availability of more substantial outcomes related to HIV care. Second, the sample size corresponds to a 10% difference between study groups under the assumption that participants will respond to the final adherence questionnaire, which may not be the case. Third, despite the stratified randomization, it may not be possible to identify if a particular subgroup will benefit more from the intervention. By doing a subgroup analysis of adherence, we will be able to assess the difference in outcomes among subgroups.

To conclude, this study will generate valuable evidence on the use and implementation of mHealth services for young people living with HIV in Peru. If effective, it could inform public policies and improve the quality of care for young people living with HIV.

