**Methods:**

A 2-arm randomized controlled trial with a parallel assignment of 1:1, with no blinding of study intervention, was performed. Eligible participants are consenting people living with HIV aged 18-29 years who receive HIV care at the study center and whose mobile phones support WhatsApp. Following informed consent and a baseline survey on clinical and personal preferences (eg, timing and frequency of messages), participants are randomized to the control group (messages designed by the research team) or to the experimental group (messages designed by participants), stratified by sex, educational level, current ART intake, and history of ART abandonment. Participants in both groups receive up to 3 WhatsApp messages per week for 16 weeks. ART adherence, the primary outcome, is measured using the Simplified Medication Adherence Questionnaire (SMAQ) at 4, 8, 12, and 16 weeks. Monthly feedback questionnaires on user experience are also administered. The WhatsApp chat format allows two-way communication between participants and the research team throughout the study. We will compare ART adherence between 2 groups at 16 weeks under the intention-to-treat principle, with no interim analysis planned. Based on an estimated 10% difference in adherence, 78.9% power, and a 2-sided α of .05, the target sample size was set at 120, later increased to 131 to include a 2-week pilot phase.

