### Study Design

A randomized controlled trial with 2 arms and a 1:1 assignment ratio will be conducted.

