### Sample Size Determination

The sample size calculus considered a 95% CI and the assumption of a 10% difference in optimal ART adherence between study groups (90% in the self-designed group versus 80% in the standardized group by the end of the study). Accounting for a power level of 78.9%, the obtained result was 120 (EPIDAT 4.0). To account for a 2-week pilot phase, we increased the sample size to 131 participants.

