### Data Analysis Plan

The primary outcome variable is ART adherence, primarily measured as a binary variable defined by the SMAQ results at 4, 8, 12, and 16 weeks of intervention. For the analysis of the primary outcome, and with an intention-to-treat approach, we will compare between both study groups the proportion of participants adherent to ART at 16 weeks of intervention with bivariate (chi-square) and multivariate (logistic regression) analyses. We will build the multivariate logistic regression model with a stepwise approach (forward selection and backward deletion), adding 1 explanatory variable at a time and starting with the explanatory variables with the highest theoretical value and strength of association with the primary outcome in bivariate analyses. At each step of model building, we will check variations in the reported odds ratios and standard errors to define the retention or removal of explanatory variables. Irrespective of bivariate association, the study group variable and potential confounders, notably history of ART abandonment, ART pick-up visits during the study period, and time of permanence in the study, will be entered into the model. We will test the final model fit with Hosmer and Lemeshow goodness-of-fit test and report results with adjusted odds ratios and 95% CIs. Preliminary outcome analyses will not be performed since they require multiple measurements, and the intervention is relatively short. We will not perform multiplicity adjustments.

With mixed models for repeated measures, we will explore the changes in ART adherence, as determined by SMAQ, from baseline to 4, 8, 12, and 16 weeks on the intention-to-treat population, with no imputation of missing data. In this model, the change from baseline value will be the dependent variable, with participant random effect and baseline ART adherence, intervention group, and measurement time as the primary fixed factors. We will check linearity assumptions for time and use participants’ unstructured covariance structure. Two-sided 95% CIs for the mean change within each study group will be calculated.

To compare the time of study permanence in both study groups, we will perform survival analysis and compare hazard ratios for study loss to follow-up between study groups, according to the study definitions. This definition lets us know how many participants are active each week of intervention.

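### Covariate odds ratios from a stepwise model with about 20 non-adherent participants cannot carry the Discussion's claim about covariate-adherence associations

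*Protocol article*

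**What the plan says.** The Data Analysis Plan compares week-16 adherence between arms by chi-square and by a multivariable logistic model. The model is built stepwise, forward and backward, one variable at a time, "starting with the explanatory variables with the highest theoretical value and strength of association with the primary outcome in bivariate analyses". At each step, changes in the odds ratios and standard errors decide what stays; no numerical rule is given. Study group and potential confounders enter whatever their bivariate association. Three confounders are named: history of ART abandonment, ART pick-up visits during the study, and time of permanence in the study. Results are reported as adjusted odds ratios with 95% CIs, and "We will not perform multiplicity adjustments".

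The Discussion then says that "our study protocol will provide valuable information on associations between several covariables, ART adherence"; the sentence goes on to include participants' experience with the intervention. The limitations paragraphs do not mention model selection or the small number of non-adherent participants.

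**The concern.** The covariates are not randomised. Where a covariate is kept because of how it behaves in the same data that estimate its odds ratio, the estimate is biased away from 1 and the nominal 95% CI no longer has its stated coverage. The bias grows as events become fewer, and here the event is non-adherence, which the design assumes to be uncommon. Each retained odds ratio is also conditional on whatever else stayed in the model, so the coefficients cannot be compared side by side as correlates.

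Two named forced terms, pick-up visits and time of permanence, are recorded after randomisation, and pick-ups lie close to adherence itself. Their odds ratios cannot be read as baseline correlates.

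At stake is the secondary claim about which factors go with adherence. The randomised comparison is not the subject of this point.

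**Working it through.** **Inputs from the protocol article.** Adherence: "90% in the self-designed group versus 80% in the standardized group by the end of the study" (Sample Size Determination). Size: "as of July 2024, we have enrolled 131 participants" (Results). Allocation 1:1 (Study Design).

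**Assumptions not in the document.** 6 to 12 candidate covariates; binary covariates of 30-50% prevalence; the true odds ratios shown below; selection either at p<0.05 or by a 10% change in the treatment log odds ratio; and, as a lower case, 105 analysed (about 20% non-response).

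**1. Events.** Mean non-adherence = (10% + 20%)/2 = 15%.
- 131 × 0.15 = 19.65
- 105 × 0.15 = 15.75

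The protocol gives no event count of its own. Its planned total of 120 would give 120 × 0.15 = 18. That total does not reproduce from its stated inputs: [1.96·√(2×0.85×0.15) + 0.803·√(0.9×0.1 + 0.8×0.2)]² / 0.10² = 194 per arm, or 388 in all, while 60 per arm gives 78.9% power for 90% versus 70%. That is a separate matter. Here it only widens the event range: 131 × 0.20 = 26.2 under 90% versus 70%, and 131 × 0.30 = 39.3 if non-adherence were 30%.

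**2. Events per term.** Study group plus three named forced covariates is four terms: 19.65/4 = 4.9, or 15.75/4 = 3.9 at n=105, before any other candidate is tried.

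**3. Smallest odds ratio that can reach p<0.05.** SE ≈ 1/√[N·p(1−p)·q(1−q)], with p = 0.15 and covariate prevalence q; threshold = exp(1.96·SE).
- q = 0.5: SE 0.489, odds ratio 2.61
- q = 0.4: SE 0.499, odds ratio 2.66
- q = 0.3: SE 0.534, odds ratio 2.85

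A significant covariate must therefore look large whatever its true effect. At 39.3 events the thresholds are still 2.11 to 2.26.

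**4. Power for one balanced covariate, n=131.** True odds ratio 2: 28%; 4: 69%; 6: 82%.

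**5. Overstatement by type of selection.** Simulation, 1,500 trials per row. Entries are the median reported odds ratio divided by the true one.

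| Setting | True OR | Forced in | Kept at p<0.05 | Kept by 10% change |
|---|---|---|---|---|
| n=131, 15% non-adherent | 1.5 | 1.03 | 2.40 | 1.39 |
| | 2 | 1.03 | 1.92 | 1.39 |
| | 3 | 1.03 | 1.52 | 1.35 |
| | 5 | 1.17 | 1.29 | 1.30 |
| n=105, 15% | 1.5 | 1.03 | 2.99 | 1.54 |
| | 2 | 1.05 | 2.25 | 1.59 |
| | 3 | 1.04 | 1.79 | 1.36 |
| | 5 | 1.16 | 1.45 | 1.33 |
| n=131, 30% | 1.5 | 1.01 | 1.82 | 1.39 |
| | 2 | 1.02 | 1.50 | 1.33 |
| | 3 | 1.03 | 1.21 | 1.25 |
| | 5 | 1.07 | 1.10 | 1.20 |

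**6. Spurious covariates, forward entry at p<0.05, about 20 events.**
- With 6 or 10 candidates, one of them real (odds ratio 2), the real factor is retained in 25-26% of trials, with a geometric-mean odds ratio of 4.3-4.6. At least one null covariate is retained in 21-35%.
- With 8 to 12 candidates, three of them real, at least one null covariate enters in 24-37% of trials, and 23-34% of retained covariates are false.
- In that second set-up, a looser p<0.20 rule raises these to 74-85% and 40-55%.

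**7. The alternative.** A Firth-penalised model with six fixed covariates, all reported, for a true odds ratio of 2: geometric mean 2.01 (n=131) and 2.06 (n=105), coverage 0.962 and 0.964, CI a factor of 2.73 and 3.12 either side of the estimate. These figures average all trials, whereas those in step 6 average only trials that kept the factor, so the contrast shows the effect of selective reporting. Penalisation alone does not explain it.

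**The case against.** The best defence is that the document states no p-value rule. Bivariate strength guides only the starting order, together with theoretical value, and retention depends on changes in odds ratios and standard errors. The nearest simple version of that, a 10% change-in-estimate rule, gives about 1.3 to 1.6-fold overstatement. This stands. A reader might infer that all reported covariate odds ratios will be at least doubled, and the documents do not support that: two-fold needs p-value-like selection and a weak true effect, it fails for a true odds ratio of 3 or more, and the forced covariates are hardly inflated.

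A reader might also infer that the stepwise model is the sole source of covariate information. It is not. Bivariate analyses, a repeated-measures model and a subgroup analysis are also planned. But the week-16 bivariate tests use the same few events, the repeated-measures model names only baseline adherence, group and time as its primary fixed factors, and the subgroup analysis is presented as a way to see which participants benefit more. None of these supplies adjusted covariate odds ratios.

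Further, covariate associations are not a listed outcome, the Discussion sentence is general, and the policy remark is tied to the intervention being effective. Misuse of the odds ratios as program advice is thus a possibility, not something the plan announces. Candidate lists and thresholds may be in an analysis plan that is not shown. That limits the point to what the article does fix: stepwise, data-driven selection with the resulting odds ratios reported.

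**Conclusion.** The point holds in limited form. The Data Analysis Plan fixes a selection method that, at the protocol's own rates, works on about 20 events, and the Discussion claims more for the covariate associations than this can give. Odds ratios of data-selected covariates are likely to be overstated, by about two-fold for true values of 1.5 to 2 under p<0.05-type selection and by about 1.3 to 1.6-fold under a change-in-estimate rule. Spurious retention in roughly 20-37% of trials applies to p<0.05 entry with 6 to 12 candidates.

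The event count is a planning value, and the candidates, true effects and thresholds are assumptions. With about 39 events the bias shrinks but does not vanish. It would be wrong to say that true associations will mostly be missed in general: that applies to modest effects (28% power at an odds ratio of 2), not to large ones (82% at 6). This is a worthwhile, inexpensive correction to a secondary claim.

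**What to change.** 1. In the Data Analysis Plan, state that the primary model serves the self-designed versus standardized comparison and that its covariate odds ratios will not be interpreted. List the adjustment variables in a table footnote.
2. If associations are wanted, add one separate exploratory model. Fix a short list of baseline covariates before analysis, for example baseline SMAQ, history of ART abandonment, current ART intake, sex, education and depression screen. Use no selection and no post-randomisation variables, fit by Firth-penalised logistic regression, and report every term with its CI as hypothesis-generating.
3. Reword the Discussion sentence to promise exploratory, imprecise estimates of baseline correlates of adherence.

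The cost is some wording and one extra model on data already collected. Data were still being curated in February 2025 according to the Results section, so the list could be fixed before analysis if that has not begun. The downside is a weaker secondary claim and wide intervals, roughly a factor of 2.7 to 3.1 either side of each estimate.

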## Methods

### Setting

In 2023, overall, 87.1%-90% of Peruvian people between 18 and 29 years of age had access to a mobile phone, with growing trends among lower socioeconomic groups [21]. The per capita country's GDP stood at US $7789.9 [22].

This study is conducted at Hospital Nacional Cayetano Heredia in Lima, Peru’s largest city and home to over 60% of people living with HIV in Peru [23]. As part of the network of health services provided by the Peruvian Ministry of Health, this hospital serves primarily people from low-resource backgrounds and provides outpatient and inpatient HIV services to over 5000 people living with HIV. Conditioned on stocks, ART is usually dispensed monthly by HIV program nurses as walk-ins on a first-come, first-served basis at the offices of the HIV program. Pregnant people living with HIV have a much closer medical follow-up than the rest of the patient population (outside children), with monthly appointments with doctors, additional counseling services at their primary care clinics, greater priority for viral load and CD4 lymphocyte testing, and regular appointments with midwives in which adherence to ART is reinforced.

Through a longstanding alliance with Instituto de Medicina Tropical Alexander von Humboldt from Universidad Peruana Cayetano Heredia, this hospital's HIV Program continuously promotes clinical and operational research.

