### Study Procedures—Implementation Phase

To preserve confidentiality, nurses from the HIV Program are informed about the study’s eligibility criteria and collaborate to identify potential participants. While they wait for infectious diseases outpatient consults or ART pick-ups, the nurses inform them about the study. For those interested, we reassess eligibility, explain the study in detail, and obtain informed consent privately (a model of our consent form is shown in Multimedia Appendix 2). Then, we fill out a REDCap baseline questionnaire, collect data to send messages through the study web-based platform, and, when applicable, explain and support the process of self-designing the messages. Figure 1 presents participant identification, recruitment, and allocation. After completing the baseline questionnaire, which provides information for stratification (sex assigned at birth, educational level, current ART intake, and previous ART abandonment), participants are randomized to one of 2 study arms allocated with a 1:1 proportion. Then, the research staff informs participants of their assigned group and provides details accordingly. Given the characteristics of the intervention, neither the researchers nor the participants are blinded.

Participants allocated to the self-designed messages group draft 10-15 messages that would help them take their ART; this number assures similitude in the number of messages received per participant in both study arms. Message creation is done during enrollment. Participants determine the final content of their messages. However, during their creation, the research staff ensures that the content excludes potentially harmful or offensive topics. If there are any doubts during the process, the staff provides support by offering examples based on characteristics identified during the baseline questionnaires and general conversation with participants (such as family, personal hobbies, goals, and other general topics). After the messages are created, the data manager reviews them and may slightly modify them to ensure clarity while keeping the original content. Once the messages are ready, the data manager enters them into the study messaging platform.

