**Figure 1 figure1:**
[figure not shown]
Participant identification, recruitment, and allocation. ART: antiretroviral therapy; REDCap: Research Electronic Data Capture; SMAQ: Simplified Medication Adherence Questionnaire.

During 16 weeks from the date of enrollment, participants receive up to 3 intervention messages per week; they are requested to reply briefly once they read those messages. Weekly, the data manager schedules the delivery of messages according to participants’ preferences, as recorded on REDCap, and monthly questionnaires. During the study, participants can chat with 2 medical doctors on the web-based study platform to ask about health issues, navigate the health system, and schedule infectious disease outpatient consultations (the standard of care requires in-person scheduling). If a participant requests modifications or additions to self-designed messages during the chat, the physician responsible for monitoring the chat will review the new messages initially. The PI will be notified if any content is deemed harmful or inappropriate. He will then contact the participant to explain the reasons for rejecting the message and will request an alternative message. This review process will continue with oversight from the data manager until the accepted messages are included in the platform’s system. Additionally, if physicians responsible for monitoring the platform identify inappropriate content during chat conversations, they will address this with all parties involved non-punitively and constructively. They will explain why the content is inappropriate and direct the conversation to ensure it remains safe and respectful.

As a follow-up, participants receive WhatsApp questionnaires every 4 weeks after enrollment and 2 days apart to assess (1) adherence to ART and (2) user experience with the intervention delivery. After 16 weeks of intervention, participants receive a final message acknowledging their participation and reminding them that the messages will stop.

Participants may withdraw from the intervention at any time by sending a message through the chat platform, responding to messages sent as part of the intervention, or contacting research team members during a medication pick-up visit. The participant will be told that withdrawing from the study does not affect their usual care at the study center. The data manager will register that patient as “withdrawn” in REDCap, and no more messages will be sent.

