### Outcomes

The primary outcome is ART adherence, measured by the SMAQ questionnaire at 16 weeks of intervention and adjusted for the effect of covariables. The SMAQ questionnaire evaluates medication adherence. It provides a dichotomic result of adherence (yes or no) and a semiquantitative estimate of adherence. >95% adherence is considered as “yes” and <95% as “no.”

The secondary outcomes are (1) ART adherence measured by the SMAQ Questionnaire at 4, 8, and 12 weeks of intervention; (2) loss to follow-up; (3) time of permanence in the study; and (4) metrics on the use of a bidirectional platform for intervention delivery.

Since the SMAQ provides a dichotomic result of adherence (yes or no), we will report the percentage of participants’ adherent to ART per study group at 4, 8, and 12 weeks of intervention.

To measure loss to follow-up, we defined it as either (1) participants not responding to messages for ≥30 continuous days since receiving the intervention and not responding to messages or questionnaires at the end of their intervention period (*t*=16), or (2) participants not responding to messages for ≥30 continuous days since receiving the intervention and not reading their messages until the end of their intervention period. We will measure it from the start of the delivery intervention until the completion of the study.

Time of permanence in the study will be measured from the first date of intervention delivery (baseline) until loss to follow-up or study completion (16 weeks). We will describe this result's median and interquartile range in both study arms.

To assess the use of the bidirectional platform, we will report frequencies, percentages, and means with an SD of messages and questionnaires programmed for sending, sent, received, read, and answered by participants. Also, the frequencies and percentages of different process indicators self-reported by participants.

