Additionally, we will perform a descriptive analysis of participants’ baseline characteristics overall and by study groups. We will also report the percentage of participants adherent to ART per study group at 4, 8, and 12 weeks of intervention. We will describe the characteristics of the intervention delivery, including the frequencies and percentages of messages received, read, and answered by participants. We will conduct all these analyses, blinding the study groups.

We will perform a thematic analysis of the most common themes in self-designed messages to evaluate relevant qualitative outcomes. In addition, we will report the median number of messages created by participants and the main reasons for adding, modifying, or eliminating messages.

We will report the results following the CONSORT-EHEALTH (Consolidated Standards of Reporting Trials of Electronic and Mobile Health Applications and Online Telehealth) statement for randomized controlled trials [25].

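### ART pick-up during the study is adjusted for in the primary model instead of being compared by arm, and the only stated check on the unblinded, self-reported outcome is likely to be sparse

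*Protocol article*

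**What the plan says.** The Outcomes section fixes the endpoint: "The primary outcome is ART adherence, measured by the SMAQ questionnaire at 16 weeks of intervention". The Discussion concedes that "we use a self-reported measurement of medication adherence". Study Procedures—Implementation Phase states that "neither the researchers nor the participants are blinded", and that "participants receive WhatsApp questionnaires every 4 weeks after enrollment", on the platform that also carries the intervention messages and the chat with study doctors. Under that section, only the self-designed arm drafts its own 10-15 messages at enrollment, with staff present.

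The stated answer to the weakness of self-report is one Discussion sentence: "We will compare SMAQ results to viral load and CD4 lymphocyte measurements when available to address this". The next sentence warns that local health-system limits may leave participants without current results. Viral load and CD4 appear neither among the outcomes nor in the Data Analysis Plan.

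ART pick-up has two uses. Data Collection describes routine counts used to size the eligible population. The Data Analysis Plan lists it among potential confounders that go into the logistic model whatever their bivariate association: "ART pick-up visits during the study period, and time of permanence in the study, will be entered into the model". The Setting section says that "ART is usually dispensed monthly by HIV program nurses", subject to stock.

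**The concern.** Participants know their arm and answer the SMAQ to the team that runs the intervention. One arm has also written the messages it receives. A pull toward favorable answers could therefore differ by arm, in the direction the trial hypothesizes. Such error enters the primary comparison directly. Masking the groups at analysis ("We will conduct all these analyses, blinding the study groups") cannot remove it, because it is already in the answers.

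A behavioral measure compared by arm would help a reader judge a SMAQ difference. The plan names one, pick-up visits, but makes it an adjustment variable. A confounder of a randomized comparison has to precede randomization. Pick-up during the 16 weeks does not, and the messages could change it.

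**Working it through.** **1. Role of pick-up.** History of ART abandonment, in the same list, is a baseline variable and a stratification factor, so adjusting for it is sound. Pick-up visits during the study are counted after allocation. Two cases show what conditioning on them does:
- If self-designed messages improve behavior, part of the effect may run through more regular collection. Comparing SMAQ at equal pick-up removes that part.
- If they change only what people report, pick-up does not differ by arm, and the SMAQ difference at equal pick-up still contains the reporting difference.

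The adjustment can thus take away real effect while leaving false effect in place. Its size cannot be computed from the documents.

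**2. What differential over-reporting could do.** The plan gives no over-reporting rate, so there is no figure to reproduce. Inputs:
- From Sample Size Determination: 80% adherence in the standardized arm, a 10-point design difference, 131 participants. From the Abstract: two-sided α of .05.
- Assumed: true adherence p = 0.80 in both arms, accurate reporting in the standardized arm, an extra share m of the non-adherent in the self-designed arm reporting adherence, a 66 vs 65 split, and everyone answering.

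Reported adherence in the self-designed arm = p + (1 − p)m, so the false difference = 0.20 × m. Rejection rates are by exact enumeration of the uncorrected chi-square test.

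| m | Reported, self-designed vs standardized | False difference | Rejection rate |
|---|---|---|---|
| 0 | 80% vs 80% | 0 | 5.0% |
| 0.10 | 82% vs 80% | 2 points | 6.0% |
| 0.25 | 85% vs 80% | 5 points | 11.8% |
| 0.50 | 90% vs 80% | 10 points | about 36% |

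At 70% true adherence, m = 0.25 and 0.50 give rejection rates of 16.4% and about 55%.

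**3. How much the stated check could show.** Assume 60 per arm (the target of 120), 85% of them SMAQ-adherent (60 × 0.85 = 51), and discordance with viral load of 10% in one arm and 20% in the other. The 95% half-width for the difference is 1.96 × √[(0.10×0.90 + 0.20×0.80)/n] = 1.96 × √(0.25/n).

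| Share with a result | n per arm | Half-width | Power |
|---|---|---|---|
| 100% | 51 | 14 points | 29% |
| 50% | 25.5 | 19 points | 17% |
| 25% | 12.75 | 27 points | 10% |

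Even split by arm, the check is weak. Those with results may also not represent the rest.

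**4. How much pick-up could show.** If pick-up followed adherence exactly, at 90% vs 80%, power at 66 vs 65 would be about 36%: the same calculation as the last row of the first table. This differs from the protocol's stated 78.9% power with 120 participants. That discrepancy is a separate matter, and nothing here rests on it.

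**The case against.** The strongest reply is that the protocol already discloses the limitation and plans a check, and that splitting the check by arm is detail for the analysis plan, which is not shown. That stands: the missing by-arm wording is not an error in itself. A reader might infer that differential over-reporting cannot be detected. The documents do not support this, since nothing prevents tabulating the planned comparison by arm. What can be said is that it is likely to be sparse and selective.

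The trial also has an active control. Both arms get up to 3 messages a week, the same chat access and the same questionnaires. This plausibly narrows any difference in reporting, though it does not remove it. The over-reporting rates above are assumptions, and at 10% the inflation is small. The documents do not show that such bias is present.

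A reader might also take pick-up as a clean objective outcome already in hand. Data Collection describes only aggregate counts. A covariate in a participant-level model does require participant-level values, but how they are captured and how complete they are is not described. Pick-up depends on stock and does not show that doses were taken. ART use is not an inclusion criterion, so the number of pick-ups due may be undefined for some participants.

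For the same reasons, a SMAQ difference without a matching pick-up difference should not be read as reporting bias. People who already collect every month may take more doses with no change in pick-up, and at about 36% power a true difference would often fail to show.

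Finally, the unadjusted chi-square comparison is untouched by the covariate choice. But the Outcomes section describes the primary outcome as covariate-adjusted, and results are to be reported as adjusted odds ratios, so the choice does affect the main result.

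**Conclusion.** The point holds in a limited form. Its firmest part is the role given to pick-up: a post-randomization measure on the adherence pathway is fixed as a covariate of the primary model. This can remove part of a real effect and leaves the more objective measure without a comparison by arm. The secondary part is that the one stated check on self-report, as written, does little about over-reporting that differs by arm.

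The possible size runs from negligible (2 points, about 6% rejection) to the whole design difference (10 points, about 36%). These figures assume 80% true adherence in both arms, over-reporting in one arm only, and full response. They illustrate what is at stake and do not estimate bias in this trial. The change should be made before the arms are compared.

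**What to change.** 1. Remove ART pick-up visits during the study from the covariates of the primary logistic model. Baseline history of ART abandonment can stay.
2. Report pick-up over the 16 weeks by randomized arm as a supportive secondary outcome, defining pick-ups due for participants on ART and stating the source and completeness of the data.
3. Tabulate SMAQ agreement with viral load and CD4 by arm, with the number in each arm who have a result.
4. Read pick-up descriptively beside the SMAQ result, with no rule that an unmatched SMAQ difference means reporting bias.

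The cost is one extra secondary analysis and one table, on data the protocol already calls for. No new participant procedure is needed. The downside is that pick-up is a coarse, stock-dependent proxy with limited power, so it can support or temper the SMAQ result but not settle it. The article's last status report, February 2025, has the data still in curation. If the arms have since been compared, the change should be labeled as made afterwards.
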